### Intervention

ABC targets one of the most important protective factors for children – the parent–child relationship. The theoretical base is social learning theory [26], with focus on how children learn from their parents and how parent behavior can promote a positive relationship. Moreover, attachment theory [27] is included in relation to child-directed play to enhance parental attunement to the child. Influence of the external environment on family functioning has been incorporated by addressing parental stress and circumstances outside the family [28,29]. ABC consists of components included in parental programs demonstrated to be effective [11,30]. Also considered, were unpublished interviews with parents about content and factors that could contribute to participation in a program, as well as interviews with potential group-leaders. Moreover, a pilot study was performed with parents in order to test the feasibility of the components.

In this study, these components are being tested with a universal approach. ABC consists of four 2.5 hour structured sessions with approximately 10 parents in each group. The sessions are held every other week with homework between the sessions. After the six-month follow-up, a booster session is offered to the parents. The themes of the four sessions are: Showing love, Being there, Showing the way, and Pick your battles. In the first session, the parents set goals that are followed-up at the last session. Short films and role plays are used to facilitate discussions in the group. Each parent receives a copy of a binder with the content of the sessions with room to take notes. In the following section, the content of the four sessions are summarized.

### Session 1. Showing love

#### Goals

The main aim of the meetings is to promote children’s development in a positive direction. As long as children live at home, the relationship with their parents is the most important factor in their development. Positive family relationships provide protection for children when exposed to stressful or harmful experiences. *My goals*: It can be helpful to look ahead to see whether what we are doing now is consistent with what kind of parents we want to be.

#### Parental factors

Children are constantly learning new things. Two ways of explaining how children learn from their parents are the *role model factor* and the *attention factor*. *The role model factor* – Your child does what you do. For example, children will copy your words, tone of voice, how you act in various situations, body language, and fears. *The attention factor* – Your child will do more of what gets your attention. Children need love and attention to develop. They quickly learn what they should do to get their parents’ attention. If children are not given enough positive attention, there is a risk they will try to get negative attention instead.

#### Showing love

Children need to feel loved. Feeling loved gives children better self-esteem and protects them in times of difficulty. Love and warmth also strengthens relationships and reduces conflict within the family unit.

#### Five to one

It is important that there is more positive attention than negative attention given for a relationship to work. Five times more love is a good balance in all relationships. If there is a great deal of conflict in the relationship, the problem might be that the child needs more positive attention.

#### Focus on what works

Recognizing and paying attention to what works leads to *virtuous cycles* and less conflict. The child will seek less negative attention and there will be more opportunities for encouragement.

### Session 2. Being there

Spending time with your child will improve the relationship and reduce conflict. *Child in charge* – *ABCD* (*see below*): Time spent with the child when the parent allows the child to lead the activity is good for the child’s development. *ABCD* also promotes better cooperation between children and parents.

**A**ctivities lead by the child

**B**oost and encourage

**C**onnect with and describe child’s actions

**D**aily activity

#### The interaction chain

The interaction chain (Table 2) is a tool to help parents understand why children behave the way they do and how adults and children influence each other’s behavior. Parents can also use the interaction chain to see how they can help the child by doing things differently *before* and *after*.

**Table 2 T2:** Description of the interaction chain at session 2

**Before**	**After**
*Preparations*	*Attention*
Prepare your child for what is going to happen.	Increase attention and encouragement when it works!
Choose an appropriate time for the activity.	
*Participation*	
Reach a joint agreement with your child on what tasks they will have.	
Give your child time to perform their tasks.	
*Positive encouragement*	
Tell your child what they should do, not what they should stop doing. For example: ‘Come sit here beside me’ instead of ‘Stop running around’.	
*Routines*	
Establish routines – do things the same way every time.	
*Positive expectations*	
Show that you believe your child is capable!	

### Session 3. Showing the way

By keeping calm during times of conflict, we model and show the way to our children, although it is not always so easy to do. All parents get angry at their children once in a while, which is normal. It is, however, important to try to handle the anger in a way that will not worsen the situation or causes more conflicts in the future.

#### Annoyance and anger

The drawbacks of shouting include: *The role model factor* - the child learns to shout; *The attention factor* - the child receives a great deal of attention when there is an argument, leading to vicious cycles and more conflicts. Further drawbacks include: *The interaction effect* - the relationship deteriorates and the family atmosphere worsens,; *The* “*cry wolf*” *effect* - sharp reprimands lose their effect, which can be dangerous in situations when your child must listen immediately to avoid danger; *The spiral effect* - an angry reprimand often triggers an angry retort.

#### Showing the way

It can be hard to always be good role models for our children, even though we do not want to get angry. There are often several things that affect how we act. A few examples:

General stress - When we are under stress, we get angry more easily. *Things you can do*: Change what can be changed. Lower your standards, or accept what cannot be changed. Make sure to schedule time for yourself for recovery and exercise.

Critical situations - Critical situations are those which lead to anger more often than others. *Things you can do*: Think about your own critical situations so that you can prepare for them.

Thoughts and physical reactions - Anger affects our bodies and how we think. It becomes more difficult to think clearly and find solutions to problems. *Things you can do*: Learn to recognize your own early signs of anger, since they are then easier to manage.

Behavior - There are drawbacks to expressing your anger in action. *Things you can do*: Take a break, anger is an emotion that will dissipate by itself if you simply wait a while. Talk about what made you angry later. Find solutions together with your child.

Consequences - What feels right and works for the moment is not always good over the long term: the short-term trap.

### Session 4. Pick your battles

When parents work together and think about which battles are important and which you can choose not to engage in, it gets easier to be consistent and things become clearer to the child. Paying more attention to what works while cutting down on nagging and reprimands will eventually lead to less conflict.

#### Natural consequences

Sometimes, as an effect of choosing not to engage in battles, your child will have to take the natural consequences instead. For instance, children often decide to wear their gloves when they realize that their hands get cold without them.

*Things will get worse before they get better*. If a parent stops nagging or reprimanding, the child may at first react more strongly in an attempt to get a reaction. If the parent can still refrain from nagging or reprimanding, the conflicts will subside.

Validate, explain, and distract - Some battles are too important to choose not to engage in. Validate, explain, and distract is a description of how you can meet your child in a manner that reduces the risk of conflict with the child.

**Validate your child’s feelings**. Show that you understand, and put the child’s feelings into words.

**Explain and repeat why**. Give your child a brief explanation for what he/she should consider.

**Distract**. Give your child something else to do and encourage that instead.

### Measures

Time points of primary interest for all outcome measures are at baseline, two weeks after intervention, and six months after baseline for both intervention and control groups. In the intervention group only, a twelve month follow-up will be conducted. A minor group of parents and children will be observed, to explore any changes in the dyadic interaction between parent and child after taking part in the ABC-program. Video recordings of both a mealtime and a play situation will be collected at baseline and at six months after baseline.

In the survey questionnaire, parents provide information about their gender, marital status, number of children, birth country, educational level, monthly income, child’s age, and gender, birth country for the child, and child care. The questionnaires included in the survey are described below.

#### Primary outcome measures

*Parental Self*-*Efficacy* (PSE) measure parents’ perception of their parenting on a 48-item questionnaire rated on an 11-point Likert scale, ranging from 0 = completely disagree to 10 = completely agree. The questionnaire is composed of 8 subscales adapted from a Tool to Measure Parenting Self-efficacy – TOPSE, which encompasses positive emotion, being with your child, empathy, guiding, rules, pressures, acceptance, and experience [31]. The questionnaire was translated into Swedish and then back-translated by an authorized translator to make sure that the original content was kept in the translation. A first draft of the questionnaire including 82 statements was tested in a pilot group of parents not participating in ABC (n = 11) who were interviewed about the content and ease of response. All parents had remarks about most of the negatively formulated items, and some of the items were considered to be unclear. The feedback from the parents was taken into account in a revised questionnaire with 34 statements removed (unpublished data).

The revised questionnaire with 48 items was tested in the pilot study of ABC including parents with children ages 1–14 years (n = 405), and analyses of internal consistency were performed. The alpha coefficients were .91 for the whole scale, and varied from .66 for the subscale pressures to .83 for the subscale being with your child.

*Child Health and Development*. To measure parent reports of children’s health and development, a questionnaire influenced by KIDSCREEN with 35 items and 6 dimensions rated on a 5-point scale to measure a child’s physical and mental health, emotional development, independence, family relations, and social competence was developed. The questions assess frequency of behavior/feelings (never-seldom-sometimes-often-always) and intensity of attitudes (not at all-slightly-moderately-very-extremely) [32]. The questions about child health and development were tested in a pilot study (n = 405). Analyses of internal reliability were computed with alpha coefficients of .92 for the total scale and subscales ranging from .73 for physical health to .87 for mental health.

#### Secondary outcome measures

*Program fidelity and delivery skills* by group leaders are measured by observations of filmed program sessions. The group leaders are rated according to two dimensions. One is regarding competence in terms of framework, speaking with own terms, being well-prepared, presenting the program in a positive manner, activating parents, strengthening parents, and interaction between the two group leaders. The second dimensions cover the content of the program including presentation of the theme, presentation of goals, dimensions of parenting, discussion of the theme, and testing at home. Group leaders are also filling in a checklist after each session containing questions on program fidelity and parental engagement.

*Parent’s use* of the method is measured through number of attended group meetings in questionnaires two weeks after each group meeting by questions about the use of program components (“yes/no”), and how it worked (“Positive/Both positive and negative/Negative”).

*Parenting Practices Interview* (PPI) [33,34] assesses retention of family rules as well as positive and negative parenting practices. In this study, the two subscales parental praise incentives, and harsh parenting were used; they were covered by 26 items, rated on a 7-point scale (from “never” to “always”, and from “not likely at all” to “extremely likely”, depending on the wording of the question). The two subscales from the PPI were tested during the development of the ABC program with a group of parents (n = 142). Analyses of internal reliability revealed that the alpha levels were .75 for parental praise and .78 for harsh parenting.

*The General Health Questionnaire*-GHQ12 [35] is included to measure the parents’ mental health, scored on a 4-point Likert scale (Positive items - “better/more than usual”, “same as usual”, “less than usual” and “much less than usual”; Negative items – “not at all” no more than usual”, rather more than usual” and “much more than usual”). The alpha level in the pilot study with 405 parents was .91.

*The Dyadic Adjustment Scale* (DAS). The brief version of the DAS covered by the subscale Dyadic Satisfaction is used to measure relational satisfaction/dissatisfaction between parents [36]. Four items on a 7-point scale, ranging from “never” to “always”, and “extremely unhappy” to “extremely happy” (dependent on the wording of the question) is used. Internal validity for the scale was .82 in the pilot study including 299 parents.

*The Emotion Regulation Questionnaire* (ERQ) evaluates the parental emotion regulation strategies [37]. This is an established and validated 10-item self-report questionnaire rated on a 7-point Likert scale (1 = strongly disagree, 4 = neutral, and 7 = strongly agree). Individuals are asked to rate the extent to which they typically try to think or behave differently in situations in order to regulate their emotions. Alpha levels were .81 for the subscale reappraisal and .74 for the subscale suppression in the pilot study with 292 parents.

A *Visual Analogue Scale* (*VAS*) is used for the health economic evaluation [38]. The health variable which will be explored to evaluate cost-effectiveness is health-related quality of life (HRQOL) in children measured by a parent-proxy VAS-scale rated from 0 to 100.

#### Observations of parent–child interaction

Video recordings of a mealtime and a play situation of the parent and child together are conducted in the home of the families. In total, 19 parents and their children are included in the observations. Concerning the mealtime, the families are asked to record a dinner, and for the play situation the families are borrowing a drawing board (Etch A Sketch) from the researchers. Parents receive instructions with the drawing board on how to use it together with the child. At both the mealtime and the play situation, the child is asked to be recorded from the front, and the parent from the front or in profile. Families who have their own video camera are encouraged to use that, or otherwise a camera is borrowed from the researchers. Observations are conducted twice: before parents participate in ABC, and about six months after first being observed.

### Analysis

Analyses will be conducted both with intention-to-treat-analyses as well as study-completer-analyses. The statistical analyses will be performed according to best practice guidelines for evaluating effects in RCTs [39]. This may come to include MANOVA, repeated measures ANOVA, and regression analyses. Cohen’s *d* will be included to calculate effect sizes. The importance of some of the parental characteristics will also be evaluated in relation to the 6-month-outcome – in other words, the moderator as well as the mediation relations. To do this, the definition by Baron and Kenny [40] for a mediational relation will be used: Evaluate 1) whether there is a significant correlation between the independent and dependent variables, 2) if the independent variable and possible mediator are significantly related, and 3) if the mediator and dependent variable are significantly related. Since the waitlist group was offered the intervention after six months, pre- to post- data for intervention and waitlist groups will also be combined to improve power in the secondary analyses.

Data collected in the trial will also be used to evaluate the possible cost-effectiveness of ABC. The cost-effectiveness analysis (CEA) [41] will include costs, savings, and health gains of the children. Calculations will be performed from the societal perspective meaning that the intention is to consider all costs and consequences. The foundation of the CEA will be an incremental analysis to investigate the extra costs, potentially extra savings and health gains of ABC in relation to the control group. The costs will include resources needed for running the ABC-program such as project staff salaries, parents’ time, materials, and meeting arrangements. The time spent on learning and performing the ABC-program will be based on information from contact persons at the local agencies involved in the study. The health gains will be reported in gained Quality Adjusted Life Years (QALYs), which will be estimated by potentially-improved scores on the HRQOL among children pre-intervention, immediately post-intervention, and 6- and 12 months post-intervention. A sensitivity analysis will be performed to explore the uncertainty of the study result.

The video-recorded observations of parents and children will be analyzed applying two different approaches. First, to explore if there are any changes in the dyadic interaction between parent and child after taking part in the ABC-program. The second approach will be to compare parental reports of parental self-efficacy as well as child health and development with observed behaviors.

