Randomization to allocate parents to intervention or control groups was performed after collection of baseline data (See Figure 2). In families where both parents announced interest to participate, both were invited to participate, but data will be pooled if their answers in the questionnaires cover the same child. Randomization was conducted at the level of individual parents for each municipality/city district: a 1:1 ratio, using SPSS version 20. However, couples were randomized together as one unit.

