### Power and sample size

The intention has been to include 300 families in the intervention and control groups respectively. According to a sample size calculation, 107 parents are needed in each group to allow a detection of an effect size of 0.4 at 90% power and the p < 0.05 level of significance, with a one-tailed test. It is also of importance to take into account the effects of a cluster design, as the intervention is offered to groups while effects of this have to be identified in intra-class correlations (ICC) [23]. The design effects of this in a universal promotion parenting program are not identified earlier, while an estimate of 0.01 could be considered as conservative. This would require a sample of 220 parents in each group [23].

Families that do not fulfill participation in the ABC will also be followed together with families attending the intervention. An attrition rate of at least 20% is expected at the 6-month follow-up after baseline, in accordance with results from somewhat similar studies [24,25]; this is why an over-recruitment will be done.

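### The analysis menu includes two complete-case methods although at least 20% attrition is expected; a baseline-adjusted mixed model would keep partial records and estimate the arm contrast directly

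*Protocol article*

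**What the plan says.** All statements are in the protocol article.

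- **Analysis.** "Analyses will be conducted both with intention-to-treat-analyses as well as study-completer-analyses". Neither set is defined. On methods: "The statistical analyses will be performed according to best practice guidelines for evaluating effects in RCTs", followed by "This may come to include MANOVA, repeated measures ANOVA, and regression analyses".
- **Measures.** Three time points are of primary interest in both arms: baseline, shortly after the programme, and 6 months after baseline. The 12-month follow-up covers the intervention arm only.
- **Power and sample size.** "An attrition rate of at least 20% is expected at the 6-month follow-up after baseline". The stated answer is over-recruitment. The same section says "Families that do not fulfill participation in the ABC will also be followed together with families attending the intervention". The calculation is that "107 parents are needed in each group to allow a detection of an effect size of 0.4 at 90% power", at the "p < 0.05 level of significance, with a one-tailed test".
- **Participants, recruitment and randomization.** "Randomization was conducted at the level of individual parents for each municipality/city district", in a 1:1 ratio. Parents were recruited in two waves, 311 and 310.

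**The concern.** Classical MANOVA and repeated measures ANOVA work on complete outcome vectors. In a three-visit design, a parent who returns the post-intervention form but not the 6-month form is dropped altogether. Unless missing scores are imputed, an intention-to-treat analysis run this way contains only parents with all three forms. It then repeats the completer analysis rather than checking it.

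Three things are at stake.

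1. **Bias.** Dropping parents with incomplete follow-up is safe only if drop-out is unrelated to outcome given what the model uses. Controls wait six months for the programme, so drop-out that differs between arms is plausible. Over-recruitment restores numbers but does not remove selection.
2. **The wrong question.** The sample size rests on a directional difference between two groups. With two arms and three visits, the group-by-time test has (2 - 1) x (3 - 1) = 2 degrees of freedom and no direction. It does not itself give an arm difference at either follow-up.
3. **Precision.** These methods treat baseline as one more outcome instead of a covariate, which wastes part of its information.

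**Working it through.** **Inputs from the article:** about 300 parents per arm; attrition of at least 20% at 6 months; d = 0.4, 90% power, one-tailed 0.05, 107 per group; 220 per group after clustering; ICC 0.01; about 10 parents per ABC group.

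**Assumptions:** baseline-outcome correlation r = 0.5 to 0.8, equal between all pairs of visits; outcomes in SD units; parents independent unless a design effect is stated.

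**1. The plan's own figure.** Two means, d = 0.4, one-sided 0.05, 90% power gives 108 per group (107.7 from the t-test version). The stated 107 is reproduced.

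**2. Rows kept.** 300 x 0.8 = 240 per arm, or 480 of 600. This is an upper limit, because attrition is given as a minimum and some parents may miss only the post-intervention form. Against no missing data, the SE rises by a factor of sqrt(300/240) = 1.118. No model recovers all of that.

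**3. SE of the 6-month effect, 240 complete parents per arm.**
- Change from baseline (the 6-month part of group-by-time): sqrt(2 x 2(1 - r)/240)
- Baseline as covariate (ANCOVA): sqrt(2(1 - r^2)/240)
- Variance ratio, ANCOVA to change: (1 - r^2)/(2(1 - r)) = (1 + r)/2
- Mixed model: 300 per arm, common baseline mean, 20% without a 6-month score. The range runs from none to all of those parents having a post-intervention score.

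| r | Change | ANCOVA | Variance ratio | Mixed model | Change / mixed | ANCOVA / mixed |
|---|---|---|---|---|---|---|
| 0.5 | 0.0913 | 0.0791 | 0.75 | 0.0791-0.0782 | 1.155-1.168 | 1.000-1.011 |
| 0.6 | 0.0816 | 0.0730 | 0.80 | 0.0730-0.0720 | 1.118-1.134 | 1.000-1.014 |
| 0.7 | 0.0707 | 0.0652 | 0.85 | 0.0652-0.0641 | 1.085-1.104 | 1.000-1.017 |
| 0.8 | 0.0577 | 0.0548 | 0.90 | 0.0548-0.0537 | 1.054-1.076 | 1.000-1.020 |

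The change contrast has an SE about 5-17% larger than the mixed model. The last column shows that partial records account for only 0-2% of this; the rest is the handling of baseline.

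**4. District.** If district explained 1-5% of outcome variance (assumed), including it would cut residual variance by about 1-5%.

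**5. Power for d = 0.4 with 240 per arm** (two-group comparison of 6-month means, one-tailed): 99.7% without clustering. With design effect 1 + 9 x 0.01 = 1.09 it is 99.5%. With the design effect implied by the plan's own figures, 220/107 = 2.06, it is 92%. A two-sided test gives 99.2% and 98.7% in the first two cases. In the third, 0.4/sqrt(2 x 2.056/240) = 3.056 and 3.056 - 1.960 = 1.096, so about 86%.

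**6. Size of a possible bias (illustration).** If 20% are lost and, in one arm only, those lost differ from completers by 0.25 to 0.5 SD, the completer contrast is off by 0.2 x 0.25 = 0.05 to 0.2 x 0.5 = 0.10 SD. That is 12.5% to 25% of the target effect of 0.4.

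**The case against.** The strongest reply is that the article commits to none of this.

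- The list is tentative and includes regression, which can carry baseline and district and needs only the visit being analysed.
- The article defers to an external guideline and does not rule out imputation or a mixed model. A full protocol or SAP may specify one, so silence on missing data is not an error in itself.
- Study-completer is undefined. If it means parents who completed the programme, the two sets differ even under complete-case analysis, because non-completing families are still followed.
- District can be entered as a factor in MANOVA or ANOVA, so its absence is not inherent to those methods.

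All of this stands, and it makes the point conditional. It does not remove it: two of the three named methods are complete-case methods, and they are named beside an expected loss of at least 20%.

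A reader might infer more, and the documents do not support it:

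- *That a complete-case intention-to-treat analysis is planned.* It follows only if MANOVA or repeated measures ANOVA is chosen and nothing is imputed.
- *That baseline would be averaged into the reported effect.* This needs the group main effect over all visits to be the test, and the article does not say that it is.
- *That row loss leaves the trial underpowered.* The power figures do not show this for the planned one-tailed test.
- *That wave was a randomization stratum.* The article gives district as the level within which parents were allocated; the waves are recruitment periods.

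**Conclusion.** The point holds in conditional form. If MANOVA or repeated measures ANOVA is used without imputation, the intention-to-treat analysis keeps at most about 240 of 300 parents per arm and largely repeats an analysis of parents with complete follow-up. It is then exposed to selective drop-out. Its group-by-time test does not estimate the difference the trial was sized for, and at r = 0.8 to 0.5 the SE of the 6-month contrast is about 5-17% larger than it need be.

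The precision loss is modest. Power for d = 0.4 stays above 90% on the one-tailed test, even at the larger design effect. The reasons to act are possible bias, the choice of contrast and the use of baseline, in a plan that leaves the primary model open. The figures rest on assumed correlations and missing-data patterns, and the size of any bias cannot be known from the document.

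**What to change.** In place of MANOVA or repeated measures ANOVA, name one primary model:

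- A likelihood-based linear mixed model for the post-intervention and 6-month scores, with parents analysed in the arm allocated.
- Baseline score as covariate, arm-by-visit terms, and municipality or city district as a fixed effect. Wave is optional.
- The arm contrast with its 95% CI at each of the two time points, since the first research question asks about both.
- A statement that the model assumes missing at random. It cannot correct for drop-out that depends on unobserved scores.
- A statement that parents with no follow-up score add nothing when baseline is a covariate. They contribute only through a version with baseline as a response and a common mean across arms, or through imputation.
- A definition of study-completer (all forms returned, or programme attended), with that analysis labelled supportive.

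The cost is analysis wording only. Baseline score, district and wave are already recorded, and no new data or visits are needed.

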### Aims

The main objective of our study is to evaluate the effects of a universal parenting program, the ABC-program, through promotion of parental self-efficacy as well as children’s development and well-being. The following research questions are investigated:

1) What effects does participation in the ABC-program have on parental skills, self-efficacy, and children’s health immediately after, and 6 months post baseline?

2) Do program fidelity and delivery by group leaders mediate the outcome of the program?

3) Are either parental level of attendance at sessions or use of program components related to effects of the program immediately, 6, and 12 months post baseline?

4) Does impact of the program differ depending on the child’s gender, age, parental ethnicity, education, income, or mental health?

5) Does parental improvement in emotion regulation or self-efficacy mediate change in children’s health and development?

6) Is the ABC-program cost-effective?

7) Is self-rated parental competence related to observed parent and child behaviors?

8) Are there changes in the interaction between parent and child?

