#### Group leader skills and fidelity

In order to study facilitator skills and fidelity to the ABC-program for group leaders, each pair of group leaders is video recorded. Before starting the group, randomization is made of which session of the total four is going to be recorded (with parental approval). Only the two group leaders are recorded visually on the video, while only the voices of participating parents are recorded; parental approval of the recordings has to be collected.

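### The printed mediation rule is three unadjusted pairwise significance checks, so it cannot tell mediation from parallel effects on two correlated parent-reported measures, and it cannot test group-leader fidelity

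*Protocol article*

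**What the plan says.** Under Analysis, the article commits to a rule: "the definition by Baron and Kenny [40] for a mediational relation will be used". It then prints the rule as three checks. The first is "1) whether there is a significant correlation between the independent and dependent variables". The other two are "2) if the independent variable and possible mediator are significantly related, and 3) if the mediator and dependent variable are significantly related". The text does not condition the third check on the independent variable or on baseline scores. It does not ask whether the direct effect shrinks once the mediator is included, and it gives no indirect effect or interval. Regression is listed among analyses that may be used, but it is not tied to mediation. The rule follows a sentence with a limited scope: "The importance of some of the parental characteristics will also be evaluated in relation to the 6-month-outcome".

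Under Aims, two research questions use the language of mediation. Question 5 asks: "Does parental improvement in emotion regulation or self-efficacy mediate change in children’s health and development". Question 2 asks: "Do program fidelity and delivery by group leaders mediate the outcome of the program". Fidelity is rated from filmed sessions. Under Group leader skills and fidelity, "each pair of group leaders is video recorded". Under Methods/Design, control parents start the program only after six months.

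**The concern.** If arm affects both the mediator and the child outcome, the two are correlated through arm even when neither influences the other. A mediator-outcome check that ignores arm counts that shared dependence as evidence of a pathway. Any further correlation between the two measures also counts. Some is plausible here, because the same parent completes the self-efficacy scale, the emotion regulation scale and the child health questionnaire. A positive answer to question 5 could then be published as a mechanism when the data show only two parallel effects. The error runs in the program's favor.

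Question 2 has a different problem. The second check relates arm to the mediator. No session is delivered to controls before the 6-month comparison, so fidelity has no control-arm value to relate to arm.

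**Working it through.** **Inputs from the article**
- Effect size 0.4 (Power and sample size). The stated 107 per group is reproduced: 2 × (1.645 + 1.282)² / 0.4² = 107.1 for one-tailed 0.05 and 90% power. The article gives no figure for the mediation rule itself.
- About 300 parents per arm (Methods/Design) and at least 20% attrition at 6 months (Power and sample size): 300 × 0.8 = 240 analyzed per arm, N = 480.
- About 10 parents per ABC group (Intervention).

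**Assumptions not in the article**
- The effect of 0.4 SD applies to both mediator M and outcome Y.
- Baseline-to-follow-up correlation is 0.7.
- Baseline correlation between M and Y, ρ, is 0 to 0.5.
- Follow-up errors are independent unless stated.
- Each check is two-sided at 0.05.
- There is no path from M to Y, so every declaration of mediation is false.

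**Checks 1 and 2.** The expected test statistic for each is 0.4 × √(240/2) = 4.38, so each passes with probability about Φ(4.38 − 1.96) = 0.99. Simulation gives about 98.5% for both together. Check 3 therefore decides.

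**Check 3, unadjusted.** With 1:1 allocation, arm adds d²/4 = 0.04 to the covariance of M and Y and to each variance. Shared baseline adds 0.7² × ρ = 0.49ρ to the covariance. The marginal correlation is r = (0.49ρ + 0.04) / 1.04, and the check passes with probability of about Φ(atanh(r) × √477 − 1.96):
- ρ = 0: r = 0.038, pass about 0.13
- ρ = 0.2: r = 0.133, pass about 0.83
- ρ = 0.4: r = 0.227, pass above 0.99

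**All three checks together, by simulation (d = 0.4)**

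| Baseline correlation | As printed, follow-up scores | As printed, change scores | Mediator path adjusted for arm and both baselines |
|---|---|---|---|
| 0 | 13% | 28% | about 5% |
| 0.2 | 82% | 51% | about 5% |
| 0.4 | 98% | 74% | about 5% |

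**Sensitivity**
- Smaller effect: with d = 0.2 on both measures, the printed rule on follow-up scores fires in about 2% of trials at ρ = 0, rising to about 36% to 39% at ρ = 0.4 to 0.5. Checks 1 and 2 then fail more often.
- Adjusting for arm alone is not enough: at ρ = 0.3 and d = 0.4, false mediation is 96.6% as printed, 88.7% adjusted for arm, and 5.4% adjusted for arm and both baselines.
- Correlated follow-up errors: at ρ = 0.3 with errors also correlated 0.3, all three versions give 98.5%.

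**Question 2.** Fidelity is observed only where sessions are held, and none is held for controls in the first six months. Check 2 cannot be computed in the randomized comparison. Within the intervention arm, fidelity varies by group or leader pair, so the information is about 300 / 10 = 30 groups, not 300 parents.

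**The case against.** The strongest reply is that the article names a published definition and condenses it into one sentence. Covariates and the estimator may sit in an analysis plan that is not shown, and silence about adjustment does not exclude it. This has some force: the text does not say that arm must be ignored. But the article prints the rule as what will be evaluated, and the printed checks omit what would separate mediation from parallel effects. That is a stated rule, not a missing detail.

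Several further objections stand and limit the claim:
- A reader might infer that the rule declares mediation whenever the program moves both measures. It does not. At d = 0.4 with no other link it does so in about 13% of trials.
- The 82% to 98% depends on assumed correlations and stability. The article reports internal consistency within scales, but no correlation between parent and child measures.
- Question 5 speaks of improvement and change. On change scores the rate is 28% to 74%, which is lower at the higher correlations but still far above 5%.
- A reader might infer that the article applies the rule to fidelity. It introduces the rule for parental characteristics. The supportable point is that no other mediation rule is given and this one cannot test fidelity.
- A reader might infer that question 2 is unanswerable. It can be studied as an association among delivered groups. Question 3 already asks about attendance in those terms.

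**Conclusion.** The concern holds as a defect in the printed rule for question 5 and in the wording of question 2. For question 5 the false-mediation rate exceeds 5% in every d = 0.4 setting examined, and it is large once the two parent-reported measures correlate for reasons other than the program. The exact size is conditional on the assumptions listed. With a small effect and no such correlation, the rate is below 5%.

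Adjustment for arm and both baselines should not be read as a full cure. Its rate of about 5% depends on independent follow-up errors. Shared-reporter error or confounding arising after baseline could bring the problem back. The stake is two of eight research questions, both explanatory. The randomized comparison on the primary outcomes does not depend on this rule.

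**What to change.** **Question 5.** Replace the three checks with an estimated indirect effect and its confidence interval. Take the mediator at the two-week post-intervention assessment and the outcome at 6 months. Adjust for arm, baseline mediator and baseline outcome, and allow for clustering by ABC group and by couple, for example by resampling those units in a bootstrap. Label the result exploratory, and say that baseline adjustment does not remove post-baseline confounding or shared-reporter error.

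**Question 2.** Reword it to ask whether group-level fidelity and delivery are associated with outcome within the intervention arm. Use a mixed model with ABC group as a random effect, describe it as observational, and state that it rests on about 30 groups. Fewer may contribute, since the Discussion reports two leader pairs without any recording and some incomplete ones.

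**Cost.** A wording change and modest extra analysis. No new measures are needed, because the required assessments are already planned. Data collection is not complete, since the 12-month follow-up is described as still to come. The sponsor should expect a less favorable or less certain mechanism claim.
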